### 4.2 Inclusion criteria

In order to be eligible to participate in this study, a subject must meet all of the following criteria:

- The patient is willing to participate and has provided written informed consent authorization before participating in the study
- The patient is  $\geq 18$  years of age at the time of consent
- The patient has sufficient understanding of the Dutch, French, or English written language
- The health status of the patient allows general anaesthesia and surgery for the removal of a cholesteatoma
- The patient is eligible to undergo a CWU tympanomastoidectomy approach based on the clinical and/or radiological suspicion for a cholesteatoma. Patients should only be included when the surgeon deems a transcanal approach not feasible and that, therefore, a mastoidectomy is necessary based on the pre-operative assessment.

### 4.3 Exclusion criteria

A potential subject who meets any of the following criteria will be excluded from participation in this study:

- Cases of revision surgery due to residual disease with a normal, intact or reconstructed tympanic membrane
- Cases where a previous obliteration has taken place
- Cases of congenital cholesteatoma
- Patient with an indication for the surgery due to a disease other than cholesteatoma (chronic otitis media)
- In rare cases patients may have a pathology which makes obliteration unavoidable due to the invasiveness of the disease (e.g. cholesteatoma extension into and near

total destruction of the bony ear canal or bony tegmen plate). This is judged by the treating physician. These patients cannot be included because randomisation is not a possibility in these cases.

- Severe comorbidity with an expected survival of less than five years
- Comorbidity or disorder which could interfere with the completion of questionnaires (e.g. known psychiatric disorder, mental retardation)
- Compromising anatomical situation (i.e. radical cavity, Congenital craniofacial anomalies with involvement of the temporal bone and including cleft palate)
- Contraindication to undergo a diffusion-weighted magnetic resonance imaging (DW-MRI) (e.g. claustrophobic, metal parts of implants in the body such as a pacemaker)

#### 4.4 Sample size calculation

To detect a clinically relevant outcome of the primary objective (residual or recurrent disease) a sample size of at least 160 participants is needed. To calculate the sample size we used applicable and recent retrospective results of the UMC Utrecht (from January 2015 to March 2020) and reported recurrence rates from a systematic review of the literature, as this represents the most methodologically comparable and robust dataset currently available. We used our results to calculate the sample size needed with a power of 0.80. Relevant clinical difference was set at 20%. The calculation is based on a two independent proportions power analysis using a Z test with pooled variance with a alpha of 0.05 and a power of 0.80. Sample size calculations were performed with PASS 2008 and resulted in 80 patients per arm. To compensate for potential dropouts, a 10% margin is implemented, **resulting in 178 patients in total.**

| Two Independent Proportions (Null Case) Power Analysis                    |                               |                               |                                     |                                   |                     |                     |                 |                 |        |
|---------------------------------------------------------------------------|-------------------------------|-------------------------------|-------------------------------------|-----------------------------------|---------------------|---------------------|-----------------|-----------------|--------|
| Numeric Results of Tests Based on the Difference: P1 - P2                 |                               |                               |                                     |                                   |                     |                     |                 |                 |        |
| H0: P1-P2=0. H1: P1-P2=D1<>0. Test Statistic: Z test with pooled variance |                               |                               |                                     |                                   |                     |                     |                 |                 |        |
|                                                                           | Sample
Size
Grp 1
N1 | Sample
Size
Grp 2
N2 | Prop H1
Grp 1 or
Trtmnt
P1 | Prop
Grp 2 or
Control
P2 | Diff
if H0
D0 | Diff
if H1
D1 | Target
Alpha | Actual
Alpha | Beta   |
| Power
0.8009                                                           | 80                            | 80                            | 0.2000                              | 0.4000                            | 0.0000              | -0.2000             | 0.0500          | 0.0472          | 0.1991 |

## 5. TREATMENT OF SUBJECTS

### 5.1 Investigational product/treatment

All subjects will undergo a canal wall up surgery to remove their cholesteatoma. Half of the cohort (group B) will undergo surgery *with* obliteration. Obliteration is to be performed using various materials: autologous bone dust, cartilage, muscle, synthetic material (Bonalive® or hydroxyapatite), or a combination of these. Only the outcomes of these two treatments (with or without obliteration) will be studied. No products will be studied.

## 6. METHODS

### 6.1 Study parameters/endpoints

#### 6.1.1 Main study parameter/endpoint

The main endpoint is the number of patients with recurrent or residual cholesteatoma. Follow-up for recurrent/residual cholesteatoma will be performed after 6-18 weeks and after approximately 1, 3 and 5 years. Follow-up is done by micro-otoscopy and DW-MRI scans (after 1, 3 and 5 years) (see figure 1 for the follow-up steps). A newly formed retraction pocket from the tympanic membrane correlates with recurrent disease (clinical diagnosis), whereas cholesteatoma formation behind a normal or an intact tympanic membrane after primary surgery correlates with residual disease (radiologic diagnosis).

#### 6.1.2 Secondary study parameters/endpoints

- **Baseline characteristics:**
  - Patient demographics (age (as collected by birthyear), gender), date of first presentation at the outpatient clinic, date of surgery, operated side (right/left), applied antibiotic treatment within in 2 weeks prior to surgery.
  - Co-morbidities and lifestyle factors: smoking, obesity, asthma, diabetes, COPD, allergies, rhinosinusitis.
  - Amount and type of all previous ear surgeries which are not mentioned in the exclusion criteria.
- **Hearing outcome:**
  - As measured by audiometric testing (pure-tone average thresholds (PTA) as calculated over 0.5, 1, 2 and 4 kHz for the air-conduction (AC) and bone-conduction (BC) and speech audiometry. This will be measured before the surgery, and at 6-18 weeks and around 1 year after surgery. The pre-operative audiogram should not have been measured more than 6 months prior to surgery.

- **Surgical characteristics:**

- A short 'standard' surgical report/template written by the participating otologists per center will be collected and used in the scientific publication to demonstrate any potential differences in surgical technique. This **does not** include patient information.
- STAMCO-classification: Localization and extension of the cholesteatoma, presence of preoperative complication status and the ossicular chain status before/at the time of removal of the cholesteatoma will be recorded. Any differences in outcomes in STAMCO classifications between the two randomized groups will be evaluated and described.

**Figure 2:** Localization, disease extension and complications as described by the STAMCO classification (18, ten Tije et al.)

[figure not shown]

- Material used for obliteration (Bonalive®, bonedust, hydroxyapatite, cartilage, muscle) as registered in the surgical report.

- Ossicular chain reconstruction (OCR); performed (yes/no), if yes, the used material and type of reconstruction (PORP, TORP, use of incus interposition, type 3 tympanoplasty) will also be reported.
- Surgical personnel: It is registered if an ENT-doctor in training (resident) or fellow has operated along with the specialist.
- Surgical time: Surgery time is recorded in minutes for each surgery and described.
- Revision surgery during follow-up: the information and observations as gathered by the surgical report will be collected from all revision surgeries performed during the follow-up of this study.
- **Complications**
  - Caused by the cholesteatoma (e.g. labyrinth fistula, dura defect, meningoencephalocele, dehiscence of facial nerve, interrupted bony tegmen plate, etc.).
  - Complications during or after surgery (e.g. wound infection, bleeding, damage to the inner ear (resulting in perceptive hearing loss or dizziness), damage to the facial nerve causing facial paralysis, damage to the taste nerve resulting in change in taste, intracranial complications (damage to the tegmen, liquor leakage), tinnitus).
  - Complications that occur within the first 6 weeks after surgery will be registered
- **Quality of life:** Is quality of life comparable between the two techniques? This will be measured using a validated patient reported outcome measure (PROM) in the form of an otological questionnaire (OQUA) and two generic quality of life questionnaires before and after the surgery (27).
  - **OQUA:** This is a otological questionnaire and includes 34 questions, covering eight major types of ear complaints (earache, pressure in the ear, hearing loss, tinnitus, otorrhoea, itch, dizziness, and loss of taste). It measures the frequency and severity of these ear complaints and the impact on quality of life.
  - **EQ5D-5L and HUI3:** The utility scores will be measured to be able to conduct an economic evaluation as described below.
- **Economic evaluation:** A cost-utility analysis will be performed according to the Dutch guideline for economic evaluations in healthcare. Differences with the Belgian guideline for economic evaluations, such the perspective, will be accounted for in the scenario analyses. For instance, in the base case, we will perform the analysis using a societal perspective. In the scenario analysis, we will include a healthcare perspective based on the Dutch base case analysis,

as well as a scenario analysis using healthcare perspective and Belgian unit costs and QoL value set. The cost-utility analysis will be performed with a lifetime time horizon. Data will be collected alongside the clinical trial and extrapolated over lifetime using a decision-analytical model. Unit costs of both procedures and of reinterventions will be calculated with a bottom-up approach using duration of surgery, personnel, disposables and materials used. Other healthcare resource use, for instance admissions, out-patient consultations, GP visits and paramedic care, will be collected using patient-reported healthcare resource use using the Institute for Medical Technology Assessment Medical Consumption Questionnaire (iMCQ). Productivity losses will be collected with the Institute for Medical Technology Assessment Productivity Cost Questionnaire (iPCQ). Both questionnaires will be adjusted for the patient population and the Belgian setting together with clinical experts and patient input. Healthcare resource use will be multiplied with unit costs from the Dutch costing manual and Belgian unit costs in a scenario analysis. The PIF is adjusted to enable validating healthcare resource use later on if necessary with claim data, such as in the IMA data linkage or VEKTIS data. For Belgian participants, the national number (RRN/INS) will be collected to enable possible data linkage with billing data from RIZIV/INAMI for validation purposes. If deemed necessary based on the trial results, approval will be requested from the competent chamber of the Information Security Committee to have the relevant study data linked with IMA data by a trusted third party (TTP, eHealth platform) using the patient national number. The national number will not be included in the trial database. This data linkage will be performed to obtain a more complete data set containing costs related to health care paid by the compulsory health insurance and the patient. This linked information will be used for the analysis of effectiveness and cost-effectiveness of the intervention.

Quality of life related to the procedures and (longer-term) hearing loss will be collected with HUI-3, specific for hearing problems. To validate use of HUI-3 in a cost-utility analyses, the EQ-5D-5L will be collected as well. Costs and quality of life will be calculated for each patient and for each health state in the decision-analytical model. Extensive sensitivity analyses will be performed, including deterministic (DSA), probabilistic sensitivity analysis (PSA), scenario analyses and VOI analyses, to estimate the impact of uncertainty on cost-effectiveness. The results of the cost effectiveness analysis will be combined with observed number eligible patients to estimate the budget impact.

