**Main study parameters/endpoints:** Rates of recurrent or residual cholesteatoma are evaluated by diffusion-weighted magnetic resonance imaging (DW-MRI) and micro-otoscopy after approximately one, three and five years. If diffusion restriction is seen on DW-MRI and/or retraction of the tympanic membrane is seen during micro-otoscopy, suspicion for recurrent or residual disease will be recorded. To confirm the diagnosis and to determine whether the cholesteatoma is either recurrent or residual, we will analyse the tympanic membrane description at the beginning of the revision surgery. All other surgical outcome measures are recorded in the surgical report. Pure tone audiograms, including air and bone conduction, and speech recognition scores are evaluated pre- and postoperatively for each patient. The EQ-5D-5L, HUI-3, iMCQ and iPCQ questionnaires will be filled in once pre- and a two times postoperatively by every patient. The OQUA will be filled in once preoperatively and three times postoperatively. The direct health-care costs will be recorded for the sponsor centre and extrapolated for the whole trial.

**Nature and extent of the burden and risks associated with participation, benefit and group relatedness:** The burden patients will experience by participating in this study will be filling in the questionnaire multiple times. The surgery, along with the imaging procedures (CT and DW-MRI), audiometry and follow-up appointments, is part of standard care and takes place irrespective of participation in this study.

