All pre-operative measurements are part of standard care in the Netherlands and Belgium. Pre-operatively patients receive an audiometric exam, a physical examination of the ear, a CT-scan and fill in the patient-reported outcome measure (PROM). Follow-up will be planned at least at 6-18 weeks, at around 1 year and at around 3 years after surgery. It is important to note that conducting a CT scan and audiometry preoperatively as well as the DW-MRI's after 1 and 3 years are part of the standard care. In line with standard care, if there is a suspicion for recurrent or residual pathology (either clinically by micro-otoscopy or radiologically by DW-MRI) the treating physician will perform a revision surgery. If during revision surgery the suspicion is confirmed, the type of recidivism (residual or recurrent) is recorded and the follow-up of the patient ends. Data that is collected up until the point of detection of residual or recurrent disease will be used for analysis (this is not an exclusion criterium). If the suspicion is not confirmed (false-positive) then the patient will continue the follow-up as planned (unless a reconstructive procedure with the goal of improving hearing has been performed). During the three years of follow-up, patients should not undergo another type of ear surgery. If this is unavoidable, as judged by the treating physicians, the patient will be retrospectively excluded. In order to ensure that the same surgical data is collected in all participating centers, a standardized operation report will be written and shared by the sponsor (UMC Utrecht). This operation report will be recorded in the electronic patient dossier (with the exception of the information if obliteration was used or not) and transferred to Castor EDC. In Castor there will be a variable to also record if obliteration has taken place or not. The only methodology that is different to standard care is the randomization of the patients and the completion of the questionnaire. It is important to note that the technique used for the obliteration technique differs slightly between centers. The exact surgical technique will be described by the participating otologists and included in the description of the study, for example in a publication.

**Figure 1.** Flowchart of the study. *Standard care is indicated by \**[figure not shown]

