### **8.1 Primary study parameter(s)**

The data of our primary outcome are quantitative and will be presented as frequencies and proportions. To compare the difference in recidivism (recurrent and residual disease) at 12, 36 and 60 months between both surgical groups the Chi-squared test or Fisher's exact test will be used. The relative risk (RR) and absolute risk difference (RD) will be calculated as effect sizes using a generalized linear model for binomial outcome with a log-link (for RR) and identity link (RD). The primary analysis will be adjusted for site by including centre as covariate in a logistic regression model with treatment arm as the main predictor. All effect sizes will be accompanied by 95% confidence intervals. To graphically demonstrate the rates of recidivism, recurrent and residual disease over the follow-up time, a Kaplan-Meier analysis will also be performed and survival curves will be constructed. Multiple imputation will be used to deal with missing

outcomes. A 20% difference is defined as the threshold for clinical relevance and will be consistently applied in both clinical effectiveness analyses and the health economic evaluation.

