### **10.5 Temporary halt and (prematurely) end of study report**

The investigator/sponsor will notify the accredited METC of the end of the study within a period of 8 weeks. The end of the study is defined as the last patient's last visit. The sponsor will notify the METC immediately of a temporary halt of the study, including the reason of such an action. In case the study is ended prematurely, the sponsor will notify the accredited METC within 15 days, including the reasons for the premature termination. Within one year after the end of the study, the investigator/sponsor will submit a final study report with the results of the study, including any publications/abstracts of the study, to the accredited METC.

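### The protocol does not secure surgical confirmation, in the trial data, of disease first suspected at the 60-month visit, and its sections differ on whether confirmation is needed for an event

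*Protocol*

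**What the plan says.** **Endpoint.** Section 6.1.1: "The main endpoint is the number of patients with recurrent or residual cholesteatoma". It does not say whether surgical confirmation is required. It calls a newly formed retraction pocket a clinical diagnosis of recurrent disease. For residual disease it says that "cholesteatoma formation behind a normal or an intact tympanic membrane after primary surgery correlates with residual disease (radiologic diagnosis").

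**Suspicion and confirmation.** In the Summary, diffusion restriction on the scan or a retraction at otoscopy means that "suspicion for recurrent or residual disease will be recorded". The next step is surgical: "To confirm the diagnosis and to determine whether the cholesteatoma is either recurrent or residual, we will analyse the tympanic membrane description" at the start of the revision operation. Section 3 agrees: "If during revision surgery the suspicion is confirmed, the type of recidivism (residual or recurrent) is recorded and the follow-up of the patient ends". It also foresees false positives, who return to planned follow-up.

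**Collection of revision findings.** Section 6.1.2, under surgical characteristics: information from the surgical report "will be collected from all revision surgeries performed during the follow-up of this study".

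**Calendar.** In Table 1 the last visit, scan and registration of recidivism are at 60 months, give or take 1 month. No later column exists. Section 10.5: "The end of the study is defined as the last patient's last visit". Section 4.1 has surgery taking place from February 2025 to July 2026 at the latest. Section 3 reserves a final year for analysis and closing the trial.

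**Analysis.** Section 8.1 uses a chi-squared or Fisher's exact test "To compare the difference in recidivism (recurrent and residual disease) at 12, 36 and 60 months between both surgical groups". Missing outcomes are to be multiply imputed.

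**The concern.** Under the Summary and section 3, the 60-month scan yields suspicions, and the operation that turns a suspicion into a confirmed and typed case comes later. The protocol schedules nothing after that scan. At 12 and 36 months there is ample follow-up left in which to confirm or refute a suspicion. At 60 months there may be none.

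The last primary time point could then be ascertained differently from the two before it. An open suspicion counted as no event loses true disease. Counted as an event, it lets in the false positives that section 3 expects, without the split into residual and recurrent disease. The first choice lowers the observed rates and, if the loss is proportional in both arms, the risk difference and the power. The effect of the second depends on the false-positive rate in each arm, which the protocol does not give.

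**Working it through.** **1. Does an event need surgical confirmation?** The Summary and section 3 say that surgery confirms and types the disease. Section 6.1.1 gives no such condition and names clinical and radiologic diagnosis. Table 1 provides for registering recidivism at the 60-month visit itself. Both readings have support, so the sections must be reconciled.

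**2. How long can a 60-month suspicion wait?** Visits run from the date of surgery.
- Last recruit (surgery July 2026): the 60-month visit falls in about July 2031. This is also about the last patient's last visit, so the time left is about 0 months.
- First recruit (surgery February 2025): the visit falls in about February 2030. February 2030 to July 2031 is about 17 months.
- If follow-up in section 6.1.2 means each patient's own schedule, which ends at 60 months, the time left is about 0 for everyone.

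So the chance of confirmation depends on the date of enrolment under the generous reading and is close to nil under the strict one.

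**3. The plan's own power figure.** Inputs from section 4.4: 0.20 v 0.40, 80 per arm, two-sided alpha 0.05, Z test with pooled variance. The statistic is Z = (p1 − p2) / √[2·p̄(1 − p̄)/80], with p̄ the mean of the two observed proportions; reject if |Z| ≥ 1.96. Summing the binomial probabilities of all rejecting outcomes gives power 0.8009 and, at a common rate of 0.40, actual alpha 0.0472. Both match the table in section 4.4. With dropout, 160 / 0.90 = 177.8, or 178. The sample size arithmetic is not in dispute.

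**4. Upper-bound illustration.** Assumptions, none of them in the protocol: 0.20 v 0.40 are the true cumulative rates at 60 months; a share f of events in each arm is first suspected at 60 months; all of these stay unconfirmed and are scored as non-events. Observed rates are then 0.20(1 − f) and 0.40(1 − f). Expected events are 80 × 0.20 + 80 × 0.40 = 48, of which 48f are lost.

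| f (assumed) | Observed rates | Difference | Events lost | Exact power, 80 per arm |
|---|---|---|---|---|
| 0 | 0.20 v 0.40 | 0.20 | 0 | 0.80 |
| 10% | 0.18 v 0.36 | 0.18 | 4.8 | 0.74 |
| 20% | 0.16 v 0.32 | 0.16 | 9.6 | 0.67 |
| 30% | 0.14 v 0.28 | 0.14 | 14.4 | 0.59 |

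**5. A milder case.** Take the trial-level reading, with recruitment uniform over 17 months and surgery 6 months after suspicion (both assumed). Only 6/17 = 35% of the late suspicions fall after the study's end. With f = 20% the lost share is 0.20 × 0.35 = 7%, the rates are 0.186 v 0.372, and exact power is 0.76.

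**6. Unequal loss.** Losing 10% of events in the obliteration arm and 20% in the control arm gives 0.18 v 0.32, a difference of 0.14 and power 0.54. Losing 20% and 10% gives 0.16 v 0.36, a difference of 0.20 and power 0.84. The direction cannot be known in advance.

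**The case against.** The strongest reply is that the text leaves confirmation open but does not exclude it. A reader might infer that disease first suspected at 60 months cannot be confirmed at all. The documents do not support that. Section 10.5 sets the end of the study at trial level, so early recruits may have more than a year. That section also concerns notification of the ethics committee and is not a database lock. A patient awaiting a revision operation could be read as still in follow-up. The sentence on revision reports is a bullet under secondary parameters. This stands as far as it goes: confirmation is possible for some patients on one reading. It is secured for none, and on that reading the last recruits still have almost no time.

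A reader might also infer that an event counts only after surgical confirmation. Section 6.1.1 and the registration row in Table 1 do not say so. That removes the certainty, but leaves sections to be reconciled on what the primary event is.

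A third tempting inference is that events suspected at 12 or 36 months drift to a later time point. That would hold only if events were dated by the operation. No section dates them so, and dating can be left to a statistical analysis plan. It forms no part of this point.

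Finally, the power losses rest on an assumed f and on losing every late case, and multiple imputation might be applied to open suspicions. The first part is right, so the figures are only an illustration. On the second, section 8.1 does not say whether an open suspicion counts as missing.

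**Conclusion.** The point holds in a limited form. The protocol fixes a last scan, a rule for collecting revision findings and an end of study that together do not secure confirmation of disease first suspected at 60 months. It also describes the event in two ways. The 60-month primary comparison could therefore miss true disease or include unconfirmed suspicions, unlike the comparisons at 12 and 36 months.

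The size is unknown, because the protocol gives no timing of detection and attaches the planned rates of 20% and 40% to no time point. The fall in exact power from 0.80 to 0.74, 0.67 or 0.59 is an upper bound for each assumed share, given equal proportional loss in both arms and late cases scored as non-events. With partial loss the effect is smaller, as in the 0.76 case. A statistical analysis plan could settle how open suspicions are analysed, but it cannot supply operation reports that the protocol did not collect.

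**What to change.** 1. **Section 6.1.1:** state whether a primary event means surgically confirmed disease, and bring the wording on clinical and radiologic diagnosis into line with the Summary and section 3.
2. **Sections 6.1.2 and 10.5:** collect the report of every revision operation prompted by a suspicion raised at or before the 60-month visit, including operations after that visit, up to a fixed cut-off before database lock and within the analysis year of section 3. Align the end-of-study definition with that cut-off.
3. **Section 8.1:** report by arm the number of suspicions still open at the cut-off, and add a sensitivity analysis that counts them as events.

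**Cost:** an amendment of wording. Section 3 describes these operations as standard care, and section 6.3 already extracts operative reports from the health record, so no study visit is added. The lock for the last patients may move by a few months, which shortens the time left for analysis in the final year.
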